#### Family stress/burden (biological family members/FSMs)

The 12-item *General Health Questionnaire* (GHQ-12) [64] is one of the most widely used and valid measures of emotional distress and is frequently used to detect the risk of psychiatric morbidity. It will be used as a measure of burden and general stress among family members and FSMs.

#### Economic evaluation (service users, biological family members/FSMs)

The *EQ-5D-5L* [65] is a generic preference-based self-report measure of health-related quality of life (HRQoL), which covers five domains: mobility, self-care, usual activities, pain/discomfort and anxiety/depression. Individuals’ responses to the EQ-5D-5L can be used to calculate a single index utility value from a tariff derived from UK population-based valuation studies. These utility values are used as the quality adjustment component in the calculation of quality-adjusted life years (QALYs) within economic evaluations. The EQ-5D-5L has been validated in diverse populations [66] and is recommended by NICE [67].

#### Working alliance (service users, family members/FSMs)

The *Working Alliance Inventory* (*WAI*)*-short-form* [68] is a 12-item self-report measure of the quality of staff-service user relationships and comprises three subscales; agreement on goals, agreement on tasks and emotional bond. The WAI short-form has good psychometric properties [69]. Working alliance has also been shown to influence outcome in therapy [70–72]. Service users will complete the WAI in relation to their key worker at the three assessment time points. Service users and family members/FSMs will also complete the WAI in relation to the therapist dyad at the end of session 3.

#### Relapse rates

Reduction in relapse will be analysed using two recognised methods [73]: (1) number and duration of inpatient admissions identified from hospital notes and (2) number and duration of exacerbations of symptoms lasting longer than 2 weeks and requiring a change in service user management such as increased observation and/or medication change by clinical team as assessed by hospital case notes. Where symptom exacerbation precedes hospitalisation, only one relapse will be recorded. Discharge rates and hospital admissions will be recorded and whether service users were discharged to higher or lower intensity services. For each participant, case notes will be examined at three time points: (i) the period 40 weeks prior to the intervention, (ii) the duration of the intervention (20 weeks) and (iii) 40-week post-intervention. Relapse will be rated retrospectively by two independent reviewers at the end of the study (at 3-month follow-up).

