## Methods/Design

### Design

This study is a feasibility cohort design, incorporating a qualitative component. The research is funded by the National Institute for Health Research (NIHR), Health Service and Delivery Research Programme (HS&DR) (12/5001/62). It was approved by North West—Greater Manchester East National Research Ethics Service (NRES) Ethics Committee (13/NW/0571).

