### Participants and recruitment procedures

*Service users* will be recruited via their care teams or self-referral from three settings within MMHSCT, which provides mental health and community services for the inner city areas of Manchester, where the majority of the city’s African-Caribbean population live [30]. Recruiting participants from acute wards, rehabilitation units and community settings facilitates inclusion of service users at differing levels of acuity and chronicity and examination of the feasibility of delivering CaFI across different clinical environments. Our rationale is that, given findings that African-Caribbean people reside in inpatient services for significantly longer periods of time than their White British counterparts [31, 32], working with families in acute as well as community settings might improve engagement and outcome is therefore likely to beneficial.

Advertisement posters and flyers will be placed in MMHSCT sites that are accessible to service users and in community locations. NIHR Clinical Research Network (CRN) Clinical Studies Officers (CSOs), who have established good relationships with care teams at MMHSCT, will support recruitment by helping to identify and recruit suitable participants. CSOs and research assistants (RAs) will visit teams at CMHTs and inpatient services to inform clinical staff about the study and inclusion criteria. Service users who are well enough (following risk assessment from care coordinator/clinical team) and have capacity to consent and give permission for their contact details to be handed to the research team will receive recruitment packs via the post. The CSO/RA will follow this up with a telephone call (at least 24 h later), where service users will be invited to meet with the RA to receive further information about the study and ask any questions. During the meeting, service users will be asked to self-ascribe their ethnicity (as this is often recorded incorrectly in case notes) and provide written informed consent. Consenting participants will be invited to complete baseline assessments in the initial meeting or an additional meeting. See Fig. 1 for CONSORT diagram detailing the recruitment procedure.

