### Inclusion/exclusion criteria

*Service users* must be of African-Caribbean descent (including those who self-identify as ‘Black-British’, ‘African-Caribbean’ or ‘mixed’ African-Caribbean but who have at least one African-Caribbean parent or grandparent). They must have a diagnosis of schizophrenia or related diagnoses (ICD F20-29) [43] and be receiving treatment through psychiatric acute or rehabilitation inpatient services or community services within MMHSCT. Service users must be 18 or older, assessed by key workers as having the capacity to consent and participate and have sufficient understanding of English language to complete measures. Those having significant cognitive impairment implicated in aetiology (e.g. organic disorder) or assessed as presenting high risk to self or others by care teams will be excluded.

*Biological family members* and *FSMs* need not be of African-Caribbean origin but must be at least 18 years old and have sufficient understanding of English language to be able to give written, informed consent and complete measures. Recruited FSMs will need to successfully complete relevant checks as detailed above.

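### The planned before-after 'reduction in relapse' cannot be read as an effect: with no treatment effect it falls for inpatient recruits, rises for community recruits, and depends overall on an unstated setting mix

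*Protocol article*

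**What the plan says.** The Relapse rates section of the protocol article states: "Reduction in relapse will be analysed using two recognised methods [73]: (1) number and duration of inpatient admissions identified from hospital notes". The second method counts symptom exacerbations that last more than two weeks and change management. Case notes are read for three windows: "the period 40 weeks prior to the intervention", then "the duration of the intervention (20 weeks) and (iii) 40-week post-intervention". Table 1 repeats these windows. The same section adds: "Relapse will be rated retrospectively by two independent reviewers at the end of the study (at 3-month follow-up".

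The Design section says: "This study is a feasibility cohort design, incorporating a qualitative component". Every participant is offered CaFI, so there is no comparator.

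On entry, the Inclusion/exclusion criteria require the person to "be receiving treatment through psychiatric acute or rehabilitation inpatient services or community services within MMHSCT". The recruitment section explains the spread of settings: "Recruiting participants from acute wards, rehabilitation units and community settings facilitates inclusion of service users at differing levels of acuity and chronicity". Neither section gives the expected split between settings.

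The only counting rule for relapse is that an exacerbation leading to hospitalisation counts once. The article does not say how an admission already under way at entry is counted. Under Data analysis, the quantitative work is descriptive, and what goes forward to a later trial is the variability of the measures.

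**The concern.** With one cohort and no control, a reduction can only mean a change within persons between windows. For someone recruited on a ward, being in hospital at entry is the qualifying state. The admission that put them there is therefore in the before-window in whole or in part, while no such admission is built into the after-window. Any of it left at entry runs into the 20-week intervention window, which takes it out of the after-window as well. Someone recruited in the community is selected for being out of hospital at entry, which pulls the other way.

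The recorded change thus reflects who was recruited as well as anything CaFI does. A figure labelled as a reduction would be easy to quote as promise of benefit, although the study cannot support that reading.

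**Working it through.** The article gives no relapse rate, length of stay, setting split or expected reduction, so there is no figure to reproduce. The check asks what the stated windows would show if CaFI had no effect.

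**Inputs from the article:** before = weeks −40 to 0; during = 0 to 20; after = 20 to 60; entry by inpatient or community care.

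**Assumptions:** 0.3, 0.6 or 1.0 admissions per year while in the community; mean stay L of 6, 12, 26 or 52 weeks; exponential times; CaFI starts at recruitment; the after-window is fully observed.

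**Formulas.** Let λ = yearly rate / 52.14, k = λ + 1/L, and π = λ/k (long-run share of time in hospital). Let A = (1 − e^(−40k))/k and B = (e^(−20k) − e^(−60k))/k.

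- Inpatient at entry: weeks in hospital before = 40π + (1 − π)A; after = 40π + (1 − π)B.
- Community at entry: before = 40π − πA; after = 40π − πB.
- Admissions started: before = (weeks in hospital before)/L; after = λ × (40 − weeks in hospital after).

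**Example (0.6 per year, L = 12).** λ = 0.011507, k = 0.09484, π = 0.1213, A = 10.307, B = 1.546, and 40π = 4.853.

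- Inpatient recruits, weeks: 4.853 + 0.8787 × 10.307 = 13.91 before; 4.853 + 0.8787 × 1.546 = 6.21 after (−55%).
- Inpatient recruits, admissions: 13.91/12 = 1.159 before; 0.011507 × 33.79 = 0.389 after (−66%).
- Community recruits, weeks: 4.853 − 0.1213 × 10.307 = 3.60 before; 4.853 − 0.1213 × 1.546 = 4.67 after (+30%).
- Community recruits, admissions: 3.60/12 = 0.300 before; 0.011507 × 35.33 = 0.407 after (+35%).

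**Range over all 12 combinations, zero treatment effect:**

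| Share recruited as inpatients | Change in admissions | Change in weeks in hospital |
|---|---|---|
| All | −81% to −50% | −78% to −18% |
| Two thirds | −73% to −21% | −71% to −8% |
| One third | −57% to +30% | −55% to +11% |
| None | +16% to +203% | +15% to +68% |

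A simulation of the same model (20,000 inpatient and 20,000 community participants per combination) gives the same ranges for all-inpatient cohorts. It gives −57% to +29% in admissions and −56% to +11% in weeks at one third, and +11% to +210% in admissions with none. At one third, both measures fall throughout with stays of 6 to 12 weeks; the fall can vanish or reverse with stays of 26 to 52 weeks.

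**Does separating the index stay restore comparability?** Not by itself. In the example, the index stay began within the before-window with probability 1 − e^(−40/12) = 0.964. That leaves 1.159 − 0.964 = 0.195 other admissions over 40 − 13.91 = 26.09 weeks at risk, or 0.0075 per week, against 0.389/33.79 = 0.0115 after. For community recruits the rates are 0.300/36.40 = 0.0082 before and 0.407/35.33 = 0.0115 after.

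**After-window.** Three months is about 13 weeks. If only these are read and counts are not scaled for exposure, 1 − 13/40 = 67.5% of the after-window is missing, which again lowers the after count.

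**The case against.** The best defence is that this is a feasibility study. No objective concerns efficacy, readmission is listed among measures whose collection is being tested, and the quantitative analysis is descriptive. No formula or test for the before-after contrast is given, and index-admission rules or person-time denominators are often left to a fuller document. The section also relies on a cited method that is not available here.

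Much of this stands, and it limits the consequence: the risk is a misleading description, not a false-positive test. It does not remove the point. The article itself names a reduction and fixes the windows and the entry routes, and together these bias the contrast even when it is only described.

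Several stronger readings are tempting but not supported:

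- *The whole cohort will show a fall.* A simple formula, f/(r × 40/52.14 + f), with f the share having an index admission before entry and r the yearly rate, suggests this: f = 1/3 and r = 0.5 give 46.5%. But it can only produce a fall. It puts every index admission's start inside the before-window and ignores that community recruits start out of hospital.
- *Inpatients are chosen because they have just relapsed.* The article's stated reason is range of acuity, chronicity and setting. A rehabilitation stay may have begun more than 40 weeks earlier; the bias then works through days in hospital, not number of admissions.
- *The change will size the next trial.* The Abstract and Data analysis carry forward variability, not an effect size.
- *The windows are unequal.* Before and after are both nominally 40 weeks; only comparisons with the 20-week window are affected.

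**Conclusion.** The point holds in this form: the change in relapse across the stated windows cannot be read as a reduction due to CaFI. For inpatient recruits a fall is expected with no effect: 50% to 81% in admissions and 18% to 78% in weeks in hospital. For community recruits a rise is expected. The overall sign is not determined by anything in the article.

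The percentages rest on the assumed rates, stays and exponential times above. The direction within each group comes from selecting people by whether they are in hospital at entry. That the contrast is before against after is inferred from the word reduction, the three windows and the absence of a control group. The remedy is a matter of wording and tabulation, and it should be made.

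**What to change.** In Relapse rates, replace the commitment to analyse a reduction with relapse and admission rates per window, reported descriptively by recruitment setting (acute, rehabilitation, community). Report the index admission separately from new admissions. Express new admissions per person-week at risk (out of hospital) and actually observed; report days in hospital separately, since that denominator does not correct them.

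Add one sentence: the change between windows will not be interpreted as an effect of CaFI or used as an effect size for the future trial. This sentence is essential, because separating the index stay does not make the windows comparable.

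Reconcile the 40-week after-window with rating at 3-month follow-up, and state how many weeks are observed per participant.

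The cost is small: number and duration of admissions and discharges are already taken from case notes. The price is that no single before-after figure can be quoted, and with 30 participants the setting subgroups will be small.

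### The before/after relapse contrast is distorted by recruiting some service users while they are inpatients, in opposite directions by setting, so the pooled change cannot be read as a reduction

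*Protocol article*

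**What the plan says.** The Relapse rates section of the protocol article sets both the measure and its direction: "Reduction in relapse will be analysed using two recognised methods [73]: (1) number and duration of inpatient admissions identified from hospital notes". The second method counts symptom exacerbations that lasted more than two weeks and led to a change in management. Case notes are read over three windows: "i) the period 40 weeks prior to the intervention, (ii) the duration of the intervention (20 weeks) and (iii) 40-week post-intervention". One counting rule is given: "Where symptom exacerbation precedes hospitalisation, only one relapse will be recorded". It says nothing about an admission already in progress at recruitment.

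On who is recruited, Participants and recruitment procedures says: "Recruiting participants from acute wards, rehabilitation units and community settings facilitates inclusion of service users at differing levels of acuity and chronicity". Under Inclusion/exclusion criteria, current treatment in acute or rehabilitation inpatient services is one of the qualifying routes. The Design section describes a single feasibility cohort, and Sample size gives 30 service users with no split by setting. Data analysis plans descriptive statistics, used to choose outcomes and estimate variability for a future trial.

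**The concern.** A person recruited on an acute ward is selected on the outcome being measured. The admission that brought them to the ward normally started within the previous 40 weeks, so at least one relapse falls in the before window because of how they were found. Nothing places an event in the later windows. Bed days are affected in the same way, because a person found on a ward is more likely to be in a long stay. Complete follow-up or adjustment for time at risk would not remove this, since the problem is selection on the before value.

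The contrast is labelled a reduction and there is no comparator. A reader of the results, or the team designing the later trial, could take relapse to be responsive to CaFI when the fall comes from the sampling. Event rates drawn from the before window would be wrong for planning.

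**Working it through.** The protocol article gives no relapse rate, length of stay, setting split or expected effect, so there is no figure to reproduce. The check asks what the stated windows show if CaFI has no effect.

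**From the document:** before window of 40 weeks ending at the start of the intervention, intervention of 20 weeks, after window of 40 weeks (weeks 20 to 60), 30 service users, inpatient and community recruits, no comparator.

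**Assumed, not in the document:** time in the community between admissions is exponential with mean C = 52, 104, 156 or 208 weeks; stay is exponential with mean L = 6, 12 or 26 weeks; no time trend; setting is defined by status at week 0; inpatient share 10% or one third; after window fully observed. Only admissions (method 1) are modelled.

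**Formulas.** Let s = 1/C + 1/L, g = (1 − e^(−40s))/s and h = (e^(−20s) − e^(−60s))/s. Expected admissions per person are:
- inpatients, before: [40 + (C/L)g]/(C + L)
- inpatients, after: (40 − h)/(C + L)
- community, before: (40 − g)/(C + L)
- community, after: [40 + (L/C)h]/(C + L)

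The chance that an inpatient's current admission began inside the before window is 1 − e^(−40/L).

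**Worked case, C = 104, L = 12.** s = 0.0929, g = 10.50, h = 1.636.
- Index admission inside the window: 1 − e^(−3.33) = 0.96.
- Inpatients: before (40 + 8.667 × 10.50)/116 = 1.129; after (40 − 1.636)/116 = 0.331, a fall of 71%.
- Community: before (40 − 10.50)/116 = 0.254; after (40 + 0.115 × 1.636)/116 = 0.346, a rise.
- Inpatient weeks among inpatients: before 12 × 1.129 = 13.5; after (40 × 12 + 104 × 1.636)/116 = 5.6.
- Pooled, one third inpatients: before (1.129 + 2 × 0.254)/3 = 0.546; after (0.331 + 2 × 0.346)/3 = 0.341; ratio 0.62. In 30 people this is 16.4 admissions before and 10.2 after.
- Pooled, 10% inpatients: before 0.342; after 0.345; ratio 1.01.

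**Range.** Ratios are after/before with no treatment effect.

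| C, L (weeks) | Inpatients before → after | Community before → after | Ratio, one third inpatients | Ratio, 10% inpatients |
|---|---|---|---|---|
| 52, 6 | 1.49 → 0.69 | 0.60 → 0.69 | 0.77 | 1.00 |
| 52, 26 | 0.91 → 0.45 | 0.31 → 0.54 | 1.00 | 1.43 |
| 104, 12 | 1.13 → 0.33 | 0.25 → 0.35 | 0.62 | 1.01 |
| 208, 6 | 1.13 → 0.19 | 0.16 → 0.19 | 0.39 | 0.73 |
| 208, 26 | 0.82 → 0.14 | 0.09 → 0.17 | 0.49 | 1.05 |

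Over all twelve combinations of C and L, inpatient admissions fall by 51-84%. The pooled ratio is 0.39-1.00 at one third inpatients and 0.73-1.43 at 10%. The index admission lies inside the window for 96% or more of inpatients at mean stays of 6-12 weeks, and for 78% at 26 weeks.

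**Would excluding the index admission repair the contrast?** In the worked case, omission alone takes the inpatient before mean to 1.129 − 0.964 = 0.165, against 0.331 after. If the before window is also moved to end just before the index admission, the person is in the community at its end, so the before mean becomes 0.254, still below 0.331. With the shifted window the pooled ratio at one third inpatients is 0.341/0.254 = 1.34. Across the assumed values the shifted rule gives a spurious pooled increase of 15-38% at mean stays of 6-12 weeks and 64-91% at 26 weeks, at either inpatient share.

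**The case against.** The strongest reply is that this is a descriptive feasibility study. No objective is to estimate an effect on relapse, no test is planned, and relapse is one of many candidate measures. A later trial would take its event rate mainly from time after baseline, which the index admission does not inflate. This stands, and it limits the harm to a misleading summary and poor planning inputs. It does not remove the point, because the article itself sets the direction, the windows and the one counting rule.

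It is also fair to say that counting the index admission is inferred from the window definition and the absence of an exclusion, and is not stated. An extraction form may deal with it. The inference is still the natural reading of "the period 40 weeks prior to the intervention".

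A reader might go further and infer that a reduction is built into the whole-cohort result, with a size set only by the number of acute-ward recruits. A simple sum that adds one forced admission per acute recruit and leaves everyone else at a constant rate supports that reading: at 0.5 admissions a year, with the index admission starting about 7 weeks before the first session, it gives a 45% fall with 10 of 30 on acute wards and 20% with 3 of 30. That sum ignores the lowered before count in community recruits. Once it is included, the pooled result at 10% inpatients can go either way, and the size depends on admission rates and stays as well as on mix.

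**Conclusion.** The point holds and should be fixed, but it does not undermine the study's feasibility aims. Among acute-ward recruits the direction is clear: admissions and bed days fall with no CaFI effect, admissions by roughly 50-85% under the assumed rates and stays. Community recruits show a smaller artefact in the opposite direction. The pooled contrast mixes the two. With no effect it ranges from about no change to a 60% reduction at one third inpatients, and from about a 30% reduction to a 45% increase at 10% inpatients. The document does not support the claim that a pooled reduction is certain, since it gives neither setting mix nor admission rates.

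For rehabilitation recruits with long stays, the admission may predate the window and then adds to duration more than to number. The figures assume a complete 40-week after window. The Relapse rates section also says "Relapse will be rated retrospectively by two independent reviewers at the end of the study (at 3-month follow-up", which does not fit a 40-week window; that is a separate matter to reconcile.

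**What to change.** - Label the admission in progress at consent as the index episode, and report its count and bed days separately from other relapses.
- Report relapses in each window separately for acute, rehabilitation and community recruits.
- Replace the wording about a reduction with relapses in each window, and state that no before/after effect will be read from them without a comparator.
- Take planning event rates for the future trial from the windows after the intervention starts, noting that everyone in this cohort receives CaFI.
- Do not present a contrast that excludes the index admission, with or without a shifted before window, as a corrected estimate.

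The cost is a field on the extraction form and a change of wording. The price in reporting is a less favourable and less simple relapse summary, with small numbers in each setting.

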**Methods/Design:**

This is a feasibility cohort design study. Over a 12-month intervention period, 30 service users and their families, recruited from hospital and community settings, will receive ten one-hourly sessions of CaFI. Where biological families are absent, access to the intervention will be optimised through ‘family support members’; trusted individuals nominated by service users or study volunteers.

We shall collect data on eligibility, uptake, retention and attrition and assess the utility and feasibility of collecting various outcome measures including readmission, service engagement, working alliance, clinical symptoms and functioning, perceived criticism, psychosis knowledge, familial stress and economic costs. Measures will be collected at baseline, post-intervention and at 3-month follow-up using validated questionnaires and standardised interviews. Admission rates and change in care management will be rated by independent case note examination. Variability in the measures will inform sample size estimates for a future trial. Independent raters will assess fidelity to the intervention in 10 % of sessions. Feedback at the end of each session along with thematically-analysed qualitative interviews will examine CaFI’s acceptability to service users, families and healthcare professionals.

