### Service user and family outcome measures

#### Psychosis symptom severity (service users)

Tables 1 and 2 show the patient and family measures used in the study and outlines the data collection schedule. The *Positive and Negative Syndrome Scale* (PANSS) [52] is a widely used 30-item semi-structured interview designed to assess positive, negative and general symptoms in service users with schizophrenic spectrum diagnoses. The PANSS has good psychometric properties of reliability and validity and is sensitive to change [52, 53]. Two trained RAs will rate the PANSS and we will report inter-rater reliability.

**Table 1 Tab1:** Patient assessment schedule

Assessment tool	Brief description	Time point			
		Duration (min)	Baseline	Post-CaFI	3-month follow-up
Socio-demographic	Socio-demographic	5	x		
PANSS	Symptoms	30–40	x	x	x
PSP	Personal and social functioning	5	x		x
PCS	Perceived criticism	5	x	x	x
Brief-IPQ	Illness beliefs	5	x		
EQ-5D	Economic evaluation	5	x	x	x
WAI—short form	Working alliance/engagement	5	x	x	x
Qualitative interview	Acceptability and feasibility	30–45			x
Total time burden			60–80	45	80–95
Session feedback forms	Acceptability	5 min end of each session			
WAI—short form Session 3	Therapeutic alliance	5 min complete during session 3			
Relapse	Case notes 40 weeks before, during and 40-week post-intervention	0 min—undertaken by independent review at 3-month FU

**Table 2 Tab2:** Family member/family support member (FSM) assessment schedule

Assessment tool	Brief description	Time point			
		Duration (min)	Baseline	Post-CaFI	3-month follow-up
Socio-demographic	Socio-demographic	5	x		
GHQ—short form	Stress/burden	5	x	x	x
KAPI—relatives^a^	Knowledge about psychosis	15–30	x	x	x
Brief-IPQ^a^	Illness beliefs	5	x		
EQ-5D	Economic evaluation	5	x	x	x
Qualitative interview	Acceptability and feasibility	30–45			x
Total time burden			35–50	25–40	55–70
WAI—short form Session 3	Therapeutic alliance	5 min complete during session 3			
Session feedback forms	Acceptability	5 min end of each session			

^a^Biological family members and nominated FSMs only (not recruited FSMs)

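### The 40-week post-intervention relapse window cannot be complete for all participants when case notes are rated at 3-month follow-up

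*Protocol article*

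**What the plan says.** The section Relapse rates defines three case-note periods: "the period 40 weeks prior to the intervention", "the duration of the intervention (20 weeks") and "40-week post-intervention". Relapse is measured by the number and duration of inpatient admissions, and by the number and duration of symptom exacerbations that last more than two weeks and change management. The stated purpose is to analyse a reduction in relapse. The section then fixes when this is done: "Relapse will be rated retrospectively by two independent reviewers at the end of the study (at 3-month follow-up").

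Table 1 repeats both elements in its relapse row. The window is "Case notes 40 weeks before, during and 40-week post-intervention", and the rating is "undertaken by independent review at 3-month FU".

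The 3-month visit follows the post-intervention assessment. The abstract gives the order: "Measures will be collected at baseline, post-intervention and at 3-month follow-up using validated questionnaires and standardised interviews". No later date for the case-note review appears anywhere.

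**The concern.** A window that runs 40 weeks past the end of therapy cannot be read from notes examined about 13 weeks past the end of therapy. The two statements sit next to each other in the text and again in Table 1, so this is unlikely to be a single slip.

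Three things are at stake.

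- **Before-after description.** The pre-intervention window is always complete and the post-intervention window is not. Any comparison that ignores observed time is tilted towards fewer relapses after therapy, and a single cohort has no control arm to reveal the tilt.
- **Planning figures.** Variability in the measures is meant to inform the sample size of a future trial. Counts from a cut-off window would misstate both level and spread for a 40-week outcome.
- **Feasibility of the measure.** One objective is to identify outcome measures and test whether they can be collected. As scheduled, this one cannot be collected as defined.

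**Working it through.** **Inputs from the protocol article**

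- Windows of 40, 20 and 40 weeks; review at 3-month follow-up (Relapse rates; Table 1).
- Recruitment of 30 service users over 9 months, about 39 weeks (Sample size).
- Therapy over about 20 weeks (Duration and intensity of therapy).
- A 12-month intervention period, 52 weeks (abstract; Therapists and training).

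**Assumptions, not in the document**

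- 3 months = 13 weeks.
- Starts spread uniformly, for the study-end readings.
- A constant relapse rate with no intervention effect, for the size of any artefact.

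**Stated figure.** The post-intervention window is 40 weeks. Observable weeks are the smaller of 40 and the time from last session to review. The stated figure is not reproduced for all participants on any reading tried.

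**Reading A: each participant reviewed at their own 3-month visit**

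- Observable: 13 weeks; 13/40 = 32.5%.
- Missing: 40 − 13 = 27 weeks, or 67.5%, for everyone.

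**Reading B: one review at study end, all therapy within 52 weeks**

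- Starts at weeks 0 to 32, last session at weeks 20 to 52, review at 52 + 13 = week 65.
- Observable time before capping: uniform on 13 to 45 weeks.
- Mean after capping at 40: (27 × 26.5 + 5 × 40)/32 = 915.5/32 = 28.6 weeks.
- Complete windows: 5/32 = 16%.
- Shortfall: 1 − 28.6/40 = about 28%.

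**Reading C: one review at study end, starts spread over 39 weeks of recruitment**

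- Last session at weeks 20 to 59, review at 59 + 13 = week 72.
- Observable time before capping: uniform on 13 to 52 weeks.
- Mean after capping at 40: (27 × 26.5 + 12 × 40)/39 = 1195.5/39 = 30.7 weeks.
- Complete windows: 12/39 = 31%.
- Shortfall: 1 − 30.65/40 = about 23%.
- This reading runs therapy to week 59, beyond the 12-month intervention period, so B fits the stated timetable better.

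**What raw totals would show with no effect.** Under a constant rate, the expected post/pre ratio equals mean observed weeks divided by 40. It does not depend on the relapse rate. The document gives no rate, so the counts below use three assumed values, with n = 30.

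| Assumed relapses per 40 weeks | Pre count | Post count, A | Post count, B | Post count, C |
|---|---|---|---|---|
| 0.25 | 7.5 | 2.4 | 5.4 | 5.7 |
| 0.5 | 15 | 4.9 | 10.7 | 11.5 |
| 1.0 | 30 | 9.8 | 21.5 | 23.0 |

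The false fall is 67.5% under A, about 28% under B and about 23% under C.

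**Check of the remedy.** With equal observed windows, or with events per observed person-week, the same constant rate gives a post/pre ratio of 1.00.

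**The case against.** The strongest reply is that the article never says raw totals will be compared. The section heading and the abstract both speak of rates. The stated windows already differ in length (40, 20 and 40 weeks), so any use of the middle period needs a time denominator. Number and duration may simply be what is extracted from the notes, with the summary statistic left to a fuller protocol or analysis plan that is not shown. This stands. A reader might infer that a reduction in relapse is bound to appear even if the intervention does nothing. The document does not support that: the artefact depends on an analysis it neither states nor rules out.

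The reply also has force on size. The wording about the end of the study, with a retrospective rating, fits a single closing review at least as well as a review at each participant's own visit. On that reading early entrants have far more than 13 weeks and some have all 40. So 67.5% is the upper end of a range, and it would be wrong to say that the window can be observed for nobody.

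Finally, this is a single-arm feasibility cohort with descriptive analysis, and none of its objectives is to show fewer relapses. A reader might infer that the before-after change will justify or size the later trial. The article says only that variability will inform sample size.

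None of this removes the conflict between window and review date. A person-time denominator removes the count artefact under a constant rate, but it does not make unobserved weeks observable. If relapse risk changes with time since therapy, the truncated rate describes mainly the early weeks.

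**Conclusion.** The inconsistency holds. The text and Table 1 both set a 40-week post-intervention window and a review at 3-month follow-up, and no reading gives all 30 participants 40 observed weeks. That conclusion does not need uniform entry: anyone who finishes therapy 13 weeks before the review has at most 13 weeks of notes after it.

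The size depends on the reading: 13 weeks for everyone, or a mean of about 28.6 to 30.7 weeks under assumed uniform entry. The false fall of about 23% to 67.5% is conditional on raw totals being compared, a constant relapse rate and no effect.

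The harm is limited to a misleading before-after description and distorted planning figures for one candidate outcome. There is no hypothesis test whose error rate would be inflated. This is a should-fix point.

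**What to change.** Reconcile the window and the review date in the section Relapse rates and in Table 1.

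- **Preferred.** Keep 40 weeks and carry out the case-note review at least 40 weeks after each participant's last session. It needs no participant contact, since Table 1 gives it zero minutes of participant time. The cost is a review about 40 − 13 = 27 weeks later than the 3-month visit. The article does not show whether the study period allows this.
- **If the timetable does not allow it.** State that the post-intervention window ends at the review date, and say whether that is one calendar date or each participant's own visit. This costs wording only, but the outcome is then no longer a 40-week one.
- **In either case.** Record the observed weeks per participant in each window, and report relapses and inpatient days per observed person-week for all three windows. Settle this before the notes are rated.

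Cutting both outer windows to 13 weeks would make them equal, but it is not preferred. It redefines the outcome. Because some participants are recruited from acute wards, a short pre-intervention window may also be weighted towards their index admission, which could produce a spurious fall of its own.
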